## Abstract

**Background:**

Hypertriglyceridemia has attracted considerable attention as a residual cardiovascular risk factor in patients with chronic kidney disease (CKD). Pemafibrate, a selective peroxisome proliferator-activated receptor α modulator, is a novel therapeutic option for hypertriglyceridemia in patients with CKD, and is associated with fewer kidney adverse events in this population compared with conventional fibrates. Although appropriate management of hypertriglyceridemia may contribute to improved kidney outcomes, evidence regarding the efficacy and safety of pemafibrate to reduce CKD progression is unknown. The aim of this study is to investigate the effect of pemafibrate on the rate of change in estimated glomerular filtration rate (eGFR) slope in patients with CKD.

**Methods:**

The Japan Kidney Association-Pemafibrate Intervention for Chronic Kidney Disease patients (JKAPI-CKD) study is a prospective, multicenter, open-label, parallel-group, randomized controlled trial. The study will enroll 2200 adults with CKD, defined as eGFR ≥20 ml/min/1.73 m^2^ and <60 ml/min/1.73 m^2^, and hypertriglyceridemia [triglyceride level ≥150 mg/dl (fasting) or ≥175 mg/dl (non-fasting)] who have not received pemafibrate or conventional fibrates within 12 weeks prior to consent. Participants will be randomized in a 1:1 ratio to the pemafibrate group (guideline-based conventional therapy plus pemafibrate 0.1–0.4 mg/day) or the control group (guideline-based conventional therapy excluding fibrates). The observation period will be 104 weeks. The primary endpoint is the chronic eGFR slope, defined as the eGFR slope from weeks 12 to 104 after study initiation.

**Results:**

On 1 December 2025, a total of 2328 participants had been enrolled, completing the participant enrollment.

**Conclusions:**

The JKAPI-CKD study is anticipated to yield novel insights into the renoprotective effects of pemafibrate in patients with CKD and establish new evidence supporting its use for the management of dyslipidemia in this population.

Trial registration: Japan Registry of Clinical Trials (jRCTs031240097)

KEY LEARNING POINTS
**What was known**:Patients with chronic kidney disease (CKD) have altered lipid profiles (high triglyceride (TG) levels, low high-density lipoprotein cholesterol (HDL-C) levels, and elevated TG/HDL-C ratio), which are associated with an increased risk of cardio-kidney events.Pemafibrate safely improves lipid profiles in patients with CKD.
**This study adds**:JKAPI-CKD is a randomized controlled trial designed to assess the effect of pemafibrate on the estimated glomerular filtration rate slope in patients with CKD.JKAPI-CKD has a large sample size (*N* = 2200) and a long follow-up period (104 weeks), enabling various analyses that may yield clinically meaningful findings.
**Potential impact**:JKAPI-CKD will yield novel insights into the renoprotective effects of pemafibrate in patients with CKD and establish new evidence supporting its use for the management of dyslipidemia in this population.

## INTRODUCTION

Patients with chronic kidney disease (CKD) are at high risk of kidney failure, cardiovascular events (CVE), and mortality [1]. Regarding treatment of dyslipidemia in patients with CKD, low-density lipoprotein cholesterol (LDL-C) lowering therapy with statins is recommended [2, 3]. Recently, hypertriglyceridemia has emerged as a novel risk factor and potential therapeutic target for reducing the risks of end-stage kidney disease (ESKD), CV outcomes, and mortality. A meta-analysis demonstrated that triglyceride (TG)-lowering therapy is associated with a reduced risk of CV outcomes and mortality rates in patients with type 2 diabetes [4]. In a randomized controlled trial (RCT) (the FIELD trial), fenofibrate reduced the decline in eGFR in patients with type 2 diabetes [5]. In another US-based national cohort study, fibrate use was associated with a lower risk of ESKD and mortality in veterans [6].

Previous large cohort studies showed that CKD patients were prone to altered lipid profiles [high TG level, low high-density lipoprotein cholesterol (HDL-C) level, and high TG/HDL-C ratio], which were associated with the incidence and progression of CKD [7–10]. In the ARIC study, hypertriglyceridemia was also a risk factor for coronary artery disease in CKD patients [11]. However, because conventional fibrates are a risk factor for kidney damage, their use in CKD patients is not recommended and is contraindicated, especially in patients with severe CKD [12]. Thus, evidence for fibrate use in CKD patients is limited.

Pemafibrate is a selective peroxisome proliferator-activated receptor alpha modulator, which lowers TG and increases HDL-C [13]. Because pemafibrate is excreted primarily in the bile, unlike conventional fibrates, its use is approved in patients with severe CKD [14]. A *post hoc* analysis of a phase III trial demonstrated that pemafibrate improved hypertriglyceridemia without significantly worsening kidney function, regardless of baseline CKD stages [15]. In a phase IV trial, no significant changes in pemafibrate pharmacokinetics were observed in patients with severe CKD compared with patients with mild-to-moderate CKD [14]. In some small observational studies in patients with CKD, switching from conventional fibrates to pemafibrate maintained a similar TG-lowering effect and led to a decrease in serum creatinine (Cr) level and an increase in estimated glomerular filtration rate (eGFR) [16, 17]. Furthermore, a large nested case-control study demonstrated that pemafibrate use, but not conventional fibrate use, was significantly associated with a decreased risk of major adverse cardiovascular events (MACE) in Japanese CKD patients [18]. Therefore, pemafibrate can be used safely in CKD patients and could slow the progression of CKD and reduce the risk of CV outcomes. However, adequately designed and well powered RCTs examining the efficacy and safety of pemafibrate in patients with CKD have not been initiated. The evidence for pemafibrate in managing dyslipidemia in patients with CKD is therefore unknown.

To address this knowledge gap, the Japan Kidney Association-Pemafibrate Intervention for Chronic Kidney Disease (JKAPI-CKD) patients Study has been designed to examine the effect of pemafibrate on kidney function (eGFR slope) in patients with hypertriglyceridemia and non-dialysis dependent CKD.

## MATERIALS AND METHODS

### Study design and study organization

The JKAPI-CKD study is a prospective, multicenter, open-label, parallel-group RCT (Fig. 1). Participant recruitment started in May 2024 and will conclude in June 2026. The scheduled study period is from May 2024 to June 2029. This study has been registered with the Japan Registry of Clinical Trials (jRCTs031240097) and is led by the Japan Kidney Association (JKA). The Kowa Company, Ltd, that manufactures pemafibrate, has provided funding for the JKAPI-CKD study through a grant to the JKA. The Steering Committee’s responsibilities comprise the preparation of the protocol, supervision of the clinical trial, review of the information and clinical trial status of each facility, and resolving issues during the study (Supplementary File 1). A biostatistician (Director of Biostatistics) and a Clinical Design Adviser will provide advice regarding the protocol and statistical analysis plan. The monitoring organization appointed by the principal investigator will regularly monitor study progress and compliance with the plan and ethical guidelines. The participating medical institutions as of 1 August 2025 are listed in Supplementary File 1. The study was approved by the Certified Review Board of Yokohama City University (CRB3180007) and will be performed in accordance with the Declaration of Helsinki and Clinical Trials Act. Written informed consent will be required from all participants before enrollment.

**Figure 1: fig1:**
[figure not shown]
Study design. Participants are patients with hypertriglyceridemia complicated by CKD. In the pemafibrate group, pemafibrate will be added to conventional treatment. In the control group, conventional treatment will be continued throughout the study period. In both groups, treatment will be ongoing in accordance with clinical guidelines, excluding fibrates. Participant assessment will begin within 8 weeks of obtaining informed consent, and the treatment period will last 104 weeks. After completion of the 104-week treatment period, participants in the pemafibrate group will discontinue pemafibrate, continue conventional treatment, and will be evaluated 8 weeks later. Participants in the control group will continue conventional treatment and will be evaluated 8 weeks after the 104-week visit. W, weeks.

### Eligibility

The JKAPI-CKD study will recruit 2200 participants with hypertriglyceridemia complicated by CKD at 497 medical institutions in Japan. Adults ≥18 years of age are eligible. Participants are also required to have CKD, determined using the most recent laboratory results from samples obtained within 16 weeks prior to consent, with CKD defined as eGFR ≥20 and <60 ml/min/1.73 m². Hypertriglyceridemia is defined as fasting serum TG level ≥150 mg/dl or non-fasting serum TG level ≥175 mg/dl at least once within 16 weeks prior to consent. Table 1 shows the eligibility criteria. The major exclusion criteria comprise the use of a fibrate or pemafibrate within 12 weeks prior to consent; pemafibrate contraindications; severe proteinuria [urinary protein-to-creatinine ratio (UPCR) >5 g/g Cr or urinary albumin-to-creatinine ratio (UACR) >3000 mg/g Cr]; severe hypertriglyceridemia (serum TG >500 mg/dl); and high creatine kinase level (>5× the upper limit of normal) using the latest measurement within 16 weeks prior to consent. Patients with severe kidney insufficiency (eGFR <20 ml/min/1.73 m^2^ within 16 weeks prior to consent), undergoing dialysis, or who have a history of kidney transplantation are also excluded (Table 1).

**Table 1: tbl1:** Inclusion and exclusion criteria.

**Inclusion criteria**
1. Age 18 years or older at informed consent
2. Patients with CKD; eGFR^a^ ≥20 ml/min/1.73 m^2^, <60 ml/min/1.73 m^2^
3. Serum TG ≥150 mg/dl (fasting), or ≥175 mg/dl (non-fasting), at least once within 16 weeks prior to consent
4. No changes in dyslipidemic medications, antihypertensive medications, or antidiabetic medications within 12 weeks prior to consent
5. Written informed consent for study enrollment obtained from the patient
**Exclusion criteria**
1. Use of fibrate or pemafibrate within 12 weeks prior to consent
2. Contraindications of pemafibrate based on the latest drug information
2–1. History of hypersensitivity to pemafibrate
2–2. Severe liver dysfunction, cirrhosis Child–Pugh class B or C, or biliary obstruction
2–3. Gallstones
2–4. Women who are pregnant, or lactating
2–5. Taking cyclosporine, or rifampin
3. UPCR >5 g/gCr, or UACR >3000 mg/gCr^a^
4. Serum TG >500 mg/dl^a^
5. Uncontrolled high blood pressure defined as SBP ≥180 mmHg, or DBP ≥110 mmHg^a^
6. HbA1c ≥8.5%^a^
7. CK > 5× ULN^a^
8. eGFR <20 ml/min/1.73 m^2^ within 16 weeks prior to consent, undergoing dialysis, or history of kidney transplantation
9. Under treatment for malignancy (except for intraepithelial neoplasia)
10. Participants in other interventional studies and clinical trials
11. Patients deemed ineligible by the investigators

a Using the latest measurement in the 16 weeks prior to consent. CK, creatine kinase; DBP, diastolic blood pressure; HbA1c: hemoglobin A1c; ULN, upper limit of normal.

### Registration and randomization

Investigators will obtain written consent from the participants after confirming that the eligibility criteria are met. This study will use an online electronic data capture system (Viedoc™ version 4 (Viedoc4); Viedoc Technologies AB, Uppsala, Sweden). Investigators will register participants using the Viedoc4 web registration system. Viedoc4 assigns a research number and treatment group for each participant. Eligible participants will be randomly allocated to the pemafibrate or control groups in a 1:1 ratio. Age (<65 years vs. ≥65 years), eGFR (<45 ml/min/1.73 m^2^ vs. ≥45 ml/min/1.73 m^2^), presence/absence of diabetes, and presence/absence of hypertension are the stratification factors because these are involved in the extent of eGFR changes.

### Treatment

#### Study treatment

Pemafibrate (immediate-release tablet or extended-release tablet) will be administered orally in the pemafibrate group within 8 weeks after enrollment. Patients in the pemafibrate group will receive pemafibrate 0.1–0.4 mg daily for 104 weeks in accordance with the latest instructions on the package insert. The pemafibrate dosage will be adjusted to achieve the TG target (serum TG level <150 mg/dl (fasting) or <175 mg/dl (non-fasting)). The maximum pemafibrate dose is 0.4 mg daily; dose reduction may be considered in patients with hepatic or kidney dysfunction. The maximum pemafibrate dose is 0.2 mg daily for patients with eGFR <30 ml/min/1.73 m^2^. In the control group, conventional treatment will be continued, with observation initiated within 8 weeks after enrollment. With rapid exacerbation of kidney function (i.e. increase in serum creatinine to ≥1.5 times the baseline value or decline in eGFR of ≥40% from baseline), marked increase in creatine kinase (≥5× the upper limit of normal), or myoglobinuria (reddish-brown urine) during the study period, pemafibrate dose reduction or discontinuation will be considered in the pemafibrate group. Investigators are advised to follow local or international practice guidelines to optimize kidney protective treatment.

#### Concomitant therapy

Treatment in accordance with relevant guidelines [2, 19] will continue for 104 weeks after enrollment in both groups. Fibrates cannot be used during the study period. In principle, change or dose adjustment of dyslipidemia medications other than pemafibrate will not be permitted during the study period. However, when an investigator decides that a change in dyslipidemia medication is unavoidable, the change must be recorded in Viedoc4. When concomitant medications that may affect kidney function, such as medications for kidney impairment, hypertension, or diabetes, or urate-lowering drugs, are also changed, the change must be recorded in Viedoc4.

#### Follow up

The study schedule is summarized in Supplementary Table 1. Follow-up visits are scheduled at 12 and 26 weeks and then every 26 weeks until 104 weeks. After 104 weeks of observation, participants in the pemafibrate group will stop taking pemafibrate and continue conventional therapy, and will be assessed 8 weeks after discontinuation. Participants in the control group will continue conventional treatment and will be assessed 8 weeks after the 104-week visit. Adherence to study treatment will be assessed by asking participants about missed doses. Blood pressure, pulse rate, and body weight measurements will be obtained at each visit. Blood and urine laboratory tests will also be performed at each visit. Laboratory parameters will be assessed using routine methods in participating medical facilities. In principle, fasting blood samples will be collected (≥10 hours after the last meal). If non-fasting blood samples are collected at baseline, non-fasting blood samples will also be collected during follow up. Details of the laboratory measurements are shown in Supplementary Table 2. LDL-C (direct method) and cystatin C will also be measured if possible (i.e. with insurance coverage). LDL-C (calculated), non-HDL-C, TG/HDL-C ratio, small dense LDL-C, TG-rich lipoprotein cholesterol, eGFR, and eGFR based on cystatin C (eGFR-cys) will be calculated using the formulas described in the Supplementary Methods (Supplementary File 2). Urinalysis will be performed on spot urine samples to assess UACR, if possible (i.e. with insurance coverage), or UPCR. At each visit, concomitant medications, cardio-kidney events, and adverse events (AEs) will be verified by the investigators.

#### Endpoints

The primary endpoint of the JKAPI-CKD study is the chronic eGFR slope from 12 to 104 weeks, thereby excluding potential acute changes in eGFR. Chronic eGFR slope is a proposed surrogate marker for kidney events [20, 21]. The key secondary endpoint is total eGFR slope calculated from randomization until week 104. Other secondary and safety endpoints are shown in Table 2. In the present study, some pre-specified subgroup analyses are planned (Supplementary Table 3), including analyses of the stratification factors used in the randomization process (baseline eGFR category, presence of diabetes, and presence of hypertension). Outcomes in the subgroups will be examined to test for interaction effects.

**Table 2: tbl2:** Outcomes.

Primary endpoint
Chronic eGFR slope from 12 to 104 weeks, after study start
**Secondary endpoints**
Key secondary endpoint
Total eGFR slope during the 104-week study period
Efficacy endpoints
Change from baseline in the following items at each visit
Lipid metabolism^a^
TG, HDL-C, TC, LDL-C, non-HDL-C, TG/HDL-C, and TRL-C
Kidney function
eGFR, Cr, UPCR, UACR, and predicted ACR^b^
Change in proportion of CKD stages between baseline and 104-week visit
Proportion of CKD stage transition between baseline and 104-week visit
Liver function
AST, ALT, γ-GTP, and ALP
Others
CK, BUN, uric acid, total protein, albumin, CRP, RBC, WBC, blood glucose^a^, Hb, Hct, platelet count, HbA1c (diabetic patients only), BNP (NT-proBNP) (heart failure patients only)
Outcomes
Incidence of composite kidney events, and components of kidney events
Incidence of composite CVEs, and components of CVEs
Incidence of rhabdomyolysis
Incidence of acute kidney injury
Physical findings
Body weight, body mass index, blood pressure (rest sitting position), pulse rate
Exploratory items
eGFR-cys, and cystatin C
Comparison of eGFR slope before the study and during the study^c^
Change from baseline in the above items at each visit and 8 weeks after 104-week visit in the cases with data available
Correlation between change in TG and other variables
Safety evaluation
Incidence of severe AEs
Incidence of AEs
Incidence of severe side-effects related to the study drug
Incidence of side-effects related to the study drug

a Lipid metabolism-related items and blood glucose analyzed separately for fasting and non-fasting blood samples.

b predicted ACR = exp 5.2659 + 0.2934 × log [min (PCR/50, 1)] + 1.5643 × log {max [min (PCR/500, 1), 0.1]} + 1.1109 × log [max (PCR/500, 1)] − 0.0773 × (if female) + 0.0797 × (if diabetic) + 0.1265 × (if hypertensive).

c eGFR slope during the study includes both chronic and total eGFR slopes. ACR, albumin-to-creatinine ratio; ALP, alkaline phosphatase; ALT, alanine aminotransferase; AST, aspartate aminotransferase; BNP, brain natriuretic peptide; BUN, blood urea nitrogen; CK, creatine kinase; Cr, creatinine; CRP, C-reactive protein; CVE, cardiovascular event; eGFR-cys, eGFR based on cystatin C; γ-GTP, gamma-glutamyl transpeptidase; Hb, hemoglobin; HbA1c, hemoglobin A1c; Hct, hematocrit; HDL-C, high-density lipoprotein cholesterol; LDL-C, low-density lipoprotein cholesterol; NT-proBNP, N-terminal pro BNP; RBC, red blood cell count; TC, total cholesterol; TRL-C, TG-rich lipoprotein cholesterol; WBC, white blood cell count.

### Statistical analysis

#### Sample size

On the basis of a previous study [20] and a guideline [21], a difference of 0.5–1.0 ml/min/1.73 m^2^/year in eGFR slope has been shown to be associated with a >97.5% probability that the drug will also reduce the risk of kidney failure. Therefore, we defined a difference of 0.5 ml/min/1.73 m^2^/year in eGFR slope between the study groups as a non-inferiority margin, assuming that the standard deviation (SD) would be 4.0 [22]. This SD estimate was based on a previous study of Japanese patients with type 2 diabetes and renal dysfunction [22]. This estimate was considered appropriate because it was derived from clinic-based real-world data in Japan, which closely reflects the multicenter clinical setting and patient characteristics of the present study. Moreover, because the JKAPI-CKD study applies rigorous inclusion and exclusion criteria (e.g. eGFR ≥20 and <60 ml/min/1.73 m² and exclusion of severe proteinuria), the study population is expected to be more homogeneous than general real-world cohorts, further supporting the validity of this assumption. The target enrollment of 2200 participants was calculated to detect a difference in the primary endpoint of 0.5 ml/min/1.73 m^2^/year eGFR slope difference with a power of 80% and an alpha error of 2.5%, accounting for a potential 10% drop-out rate.

#### Analysis set

Three analysis populations are defined for this trial: (i) the full analysis set (FAS), defined as all eligible participants who received at least one dose of the study treatment and had at least one observation in the protocol therapy period for the analysis endpoint; (ii) the per-protocol set, defined as participants in the FAS, without significant violation of the study protocol; and (iii) the safety analysis set, defined as participants who received the study drug at least once. The main efficacy analyses will be performed using the FAS population data.

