### Safety analysis

The safety analysis will be performed using data for the safety analysis set population. AEs during the study period will be summarized using frequency counts and percentages, with 95% CIs calculated by the Clopper–Pearson method. Serious AEs and treatment-related AEs will be summarized similarly. All AEs will be graded for severity in accordance with the Common Terminology Criteria for Adverse Events, version 5.0.

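### As worded, the safety set contains no control participants, and the full analysis set either shuts out controls or drops only pemafibrate non-starters

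*Protocol article*

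**What the plan says.** The *Analysis set* section of the protocol article defines three populations.

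- The FAS is "all eligible participants who received at least one dose of the study treatment and had at least one observation" for the endpoint during the therapy period.
- The per-protocol set is the part of the FAS without significant protocol violations.
- The third is "the safety analysis set, defined as participants who received the study drug at least once".

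On their use, *Analysis set* states: "The main efficacy analyses will be performed using the FAS population data". *Safety analysis* states: "The safety analysis will be performed using data for the safety analysis set population".

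The comparator is described in the Abstract (Methods) as "the control group (guideline-based conventional therapy excluding fibrates") and under *Study treatment*: "In the control group, conventional treatment will be continued, with observation initiated within 8 weeks after enrollment". No placebo is given. In the other arm, pemafibrate "will be administered orally in the pemafibrate group within 8 weeks after enrollment".

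The term *study treatment* is not defined. The section with that heading describes both arms, whereas *Follow up* ties the term to drug intake: "Adherence to study treatment will be assessed by asking participants about missed doses".

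**The concern.** Both definitions depend on receiving a dose, but only one arm is given something new to take. An analysis set should be built by a rule that both arms can meet in the same way. Otherwise membership depends on allocation and on what happens after it.

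Two things are at stake.

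- **Safety.** In patients with CKD, many of them likely to have other illness, background AE rates are hard to interpret without a concurrent control rate.
- **Primary analysis.** The non-inferiority and superiority tests on chronic eGFR slope would be run on a set that may have lost participants from the pemafibrate arm only, after an unblinded allocation.

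The per-protocol set is nested in the FAS, so none of the three stated sets is guaranteed to hold everyone randomised.

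**Working it through.** **Safety set.** Membership requires the study drug. Controls get conventional therapy without fibrates and without placebo. *Safety analysis* uses this set, and no other rule admits controls. Followed as written, the set holds 0 controls. Enrolment closed at 2328 (*Results*); split evenly that is 2328/2 = 1164 controls whose AEs are verified at each visit (*Follow up*) but who belong to no safety population. Table 2 lists AE incidence separately from drug-related side-effects, so the AE endpoint is not specific to the drug arm.

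**FAS, two readings.**

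1. *Study treatment* means pemafibrate, as the missed-dose sentence suggests. No control qualifies, and the comparison in *Efficacy analysis* cannot be run.
2. Conventional therapy counts, as the shared section heading suggests. Controls meet the dose condition automatically because their therapy simply continues. Pemafibrate-arm participants must actually start, within a window of up to 8 weeks after enrolment. The dose condition then acts on one arm only. The one-observation condition acts on both.

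These readings are alternatives; they cannot both apply.

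**Planning figures (*Sample size*).** Margin 0.5, SD 4.0, power 80%, alpha 2.5% (read as one-sided, matching the 95% CI rule), drop-out 10%.

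- n per arm = 2 × (1.960 + 0.842)² × 4.0² / 0.5² ≈ 1005, so 2010 in total.
- With drop-out: 2 × 1005/0.9 gives 2234 when each arm is rounded up; 2010 × 1.1 = 2211. Both agree with the stated 2200 to within 2%.
- With 990 per arm (1100 × 0.9), power is 79.4% and SE = 4.0 × √(2/990) = 0.18.

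The stated target reproduces and is not affected by this point.

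**Illustrative size under reading 2.** The article gives no non-starter rate and no slope for non-starters, so both are assumed. If a proportion p never start, and their mean slope differs from that of starters by g, then

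shift in arm mean = starters' mean − all-randomised mean = p × g.

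| p | g = 1 | g = 2 | g = 3 |
|---|---|---|---|
| 1% | 0.01 | 0.02 | 0.03 |
| 2% | 0.02 | 0.04 | 0.06 |
| 5% | 0.05 | 0.10 | 0.15 |
| 10% | 0.10 | 0.20 | 0.30 |

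The range 0.01 to 0.30 is 2% to 60% of the 0.5 margin. The middle case, p = 5% and g = 2, gives 0.10: 20% of the margin, or 0.10/0.18 ≈ 0.56 SE. If non-starters decline faster, the shift favours pemafibrate, and at a true difference of −0.5 the chance of falsely concluding non-inferiority rises from 2.5% to Φ(−1.96 + 0.56) ≈ 8%. If they decline more slowly, the shift goes against pemafibrate.

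The lost numbers matter little: for 1% to 10% non-starters at N = 2200, power falls from 79.4% to between 79.2% and 77.2%.

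**The case against.** Several parts of the opposing case stand.

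- **A FAS without controls is not what the authors intend.** The FAS text says study treatment, whereas only the safety set says study drug, and every primary comparison is planned against the control group. A reader might infer that both sets require the study drug and that the primary analysis is therefore impossible. The documents do not support that; they support an undefined term with one unworkable and one workable reading.
- **Not all safety information loses its comparator.** A reader might infer that kidney injury, muscle and liver findings would be reported for pemafibrate alone. Table 2 lists acute kidney injury, rhabdomyolysis, CK and liver enzymes as secondary endpoints, and *Efficacy analysis* provides for group comparisons of these. What is lost is the control reference for general and serious AEs. Those summaries are descriptive, with Clopper–Pearson intervals and no stated between-arm test.
- **The word *eligible* is not shown to be a post-randomisation exclusion.** *Registration and randomization* has eligibility confirmed before allocation, so the word may describe everyone randomised.
- **At-least-one-dose sets are common**, and the observation condition applies to both arms and is partly unavoidable: someone with no eGFR in the analysis window adds no outcome to the slope model.
- **Keeping non-starters is not free in a non-inferiority test**, because it pulls a true difference towards zero.

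It can also be said that a condensed article leaves such detail to a fuller document. That would answer an omission. Here the definitions are given, and followed as written they produce the problem.

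**Conclusion.** The point holds in two parts of unequal strength.

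The safety-set defect follows directly from the text: no control can enter, so the AE and serious AE tables have no control reference although the article describes AE checks at each visit without limiting them to one arm.

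The FAS defect is real but its size is unknown. On the only workable reading, the dose condition is a one-sided exclusion after randomisation in an open-label trial. The 0.10 shift (20% of the margin) rests on an assumed 5% non-starter rate and an assumed slope gap of 2, and on non-starters staying in follow-up and supplying eGFR values. If few fail to start, or those who do also leave follow-up, the effect is small. A reader might infer that the primary result is biased towards pemafibrate by a known amount; the article gives neither the amount nor the direction.

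**What to change.** 1. **Safety set:** all randomised participants with any follow-up after the start of treatment (pemafibrate) or of observation (control), grouped by treatment actually received, with AEs counted from the corresponding start point in each arm. Say how events in pemafibrate-arm participants who never start are shown, since they have no treatment start.
2. **FAS:** all randomised participants, analysed as randomised, whether or not the drug was started, using all eGFR values collected. Report by arm the number with no eGFR value in the analysis window; the slope model cannot supply outcomes for them.
3. **Per-protocol set:** keep it as a supporting analysis for non-inferiority and show it beside the primary result.

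The cost is wording only. AEs and eGFR are already scheduled at each visit, and the study period runs to June 2029, so the change can precede the analysis.

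The drawback is dilution. For example, if the true difference among starters were −0.5 and 5% of the arm never started and declined like controls, the all-randomised difference would be 0.95 × (−0.5) = −0.475. That is a shift of 0.025, or 5% of the margin, towards non-inferiority, which is why the per-protocol result belongs beside it.
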